#### Visits and follow-ups

There will be four visits for the recruited participants during the trial. At the first visit, research investigators will perform the enrollment by checking the eligibility screening, informed consent form, and allocation plan. Then, the blood, saliva, stool, and skin samples will be collected as a baseline and start the treatment as day 1. The next visits will be to assess the adverse drug reaction by a medical officer. At week 6, the blood samples will be collected for assessing the pharmacokinetic parameters. Week-12 visit will be the last visit at which all the participants will be assessed for any adverse reaction, and the blood, saliva, stool, and skin samples will be collected as post-treatment samples.

After the trial, patients will be asked to stop taking cannabis oil from any sources. They will be monitored for another month for withdrawal symptoms.

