## Abstract

**Background:**

In a pilot study using both cannabidiol (CBD) and tetrahydrocannabinol (THC) as single agents in advanced cancer patients undergoing palliative care in Thailand, the doses were generally well tolerated, and the outcome measure of total symptom distress scores showed overall symptom benefit. The current study aims to determine the intensity of the symptoms experienced by breast cancer patients, to explore the microbiome profile, cytokines, and bacterial metabolites before and after the treatment with cannabis oil or no cannabis oil, and to study the pharmacokinetics parameters and pharmacogenetics profile of the doses.

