### Summary of the study

Hence, the current randomized study aims to explore the efficacy of Thai cannabis oil products on the QoL of individuals diagnosed with breast cancer and treated with chemotherapies, along with the study of microbial alteration and diversity by cannabis and pharmacokinetic measures among those patients. We aim to determine the intensity of the pain and QoL experienced by cancer patients using the ESAS and the EQ-5D-5 L forms, respectively, to explore the microbiome profile, cytokines, and bacterial metabolites in hormone-dependent and independent breast cancer patients before and after the treatment with the cannabis oil or no cannabis, and to study the pharmacokinetics parameters and pharmacogenetics profile.

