#### Patient enrollment and recruitment

Patient demographic information will be reviewed by physicians using KCMH’s database. Online (e.g., on Facebook) and onsite poster (e.g., at KCMH) will be used to advertise the study. Patients will be recruited using the inclusion and exclusion criteria. The medical record database will be used to collect clinical and laboratory investigation data related to hormonal breast cancer subtypes, baseline symptoms, current medication including chemotherapy regime and other herbal use, emetic condition, history of surgery, history of other cancers, and history of radiotherapy.

For the recruitment, we will give the trial information to potential participants using surgeons and nurses in each surgical ward or outpatient clinic and a participant information sheet to confirm the participant’s understanding of the trial objective, procedure, benefits, and risks. If potential participants are willing to participate in the trial, they will be asked to sign an informed consent form with the understanding that they can quit the test at any time without any consequence.

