#### Patient allocation and blinding

The recruited patients will be randomly allocated into 3 groups: Ganja Oil (THC 1.701 mg/mL or 0.068 mg/drop; CBD 0.003 mg/mL or 0.0001 mg/drop; CBN 0.170 mg/mL or 0.007 mg/drop; COA Ganja Oil TRCM65/05232), Metta Osot (THC 77.622 mg/mL or 3.105 mg/drop; CBD 6.737 mg/mL or 0.2695 mg/drop; CBN 7.406 mg/mL or 0.296 mg/drop; COA Metta Osot TRCM64/33,743 Rev.1), and placebo oil (THC 0 mg/mL or 0 mg/drop; CBD 0 mg/mL or 0 mg/drop; CBN 0 mg/mL or 0 mg/drop; COA Placebo TRCM64/33,742) groups. The allocation will be conducted with a 1:1:1 ratio using block randomization with a block of six by the table of random numbers for creating randomization ID. The research team will provide the randomization code in an opaque envelope to conceal allocation, mask clinicians, data collectors, and patients. Following the cannabis practice patterns of the preliminary study [29], all the participants will be received cannabis or placebo oil once per day before bedtime for 12 weeks.

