#### Determination of pharmacokinetic and pharmacogenetic parameters

The kinetic concentrations of THC and CBD will be quantitatively measured in two visits to determine the pharmacokinetic and the candidate genes for pharmacogenetic parameters.

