## Discussion

Thailand actively launched cannabis oil in the market in 2018, subsequently, the FDA (Food and Drug Administration) authorized all hospitals running under the Public Health Ministry for medical cannabis to be available on prescription to patients for approved conditions like cancer chemotherapy for relief of pain, to counter inflammation, and so on [32]. The previous clinical trial as nationwide has been approved the effectiveness of the cannabis oil in cancer patients. The current study is a continual clinical trial to obtain additional information and it is expected to improve the chemotherapy-related symptoms, their QoL, and the adverse effects in breast cancer patients.

As some studies have observed distinct gut bacterial and fungal profiles in various breast cancer subtypes [15, 16], our anticipation is to identify a comparable microbial abundance pattern in both hormone-dependent and independent breast cancer patients. Additionally, we aim to detect alterations in these patterns before and after treatment with cannabis oil and placebo oil, with a focus on pain scores. A noteworthy aspect of this study is its comprehensive examination of the microbiota, encompassing the gut, skin, and oral microbiomes in breast cancer patients.

An advantageous aspects of this study are the effective observation of the immunomodulatory role of the microbiota measuring interleukin-17 (IL-17) and interferon-γ (IFN-γ), interleukin-10 (IL-10) and tumor growth factor-β (TGF-β) and the assessment of the alterations at both the baseline and post-treatment stages or within each treatment group. This approach is expected to yield specific insights into cytokine expression in breast cancer patients and reveal improvement following treatment.

The levels of Lipopolysaccharide-binding protein (LBP) and soluble CD14 (sCD14) serve as markers for bacterial translocation, indicating the potential existence of a gut-breast cancer microbiota axis [33]. It is essential to assess the influence of cannabis oil on preventing the bloodstream transmission of oncogenic bacteria through this axis. Additionally, equol, a potent estrogenic metabolite produced by intestinal bacteria [34], Is of interest. The study also aims to establish a distinct profile of bacterial markers in breast cancer patients and gain insights into their characteristics following treatment.

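### The listed eligibility criteria admit current users of cannabis oil, and no rule on outside cannabis is stated for weeks 0-12, so the placebo arm and the week-0 samples may not be cannabis-free

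*Protocol article*

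**What the plan says.** **The contrast.** The Abstract describes comparisons "before and after the treatment with cannabis oil or no cannabis oil", and Summary of the study repeats it as "before and after the treatment with the cannabis oil or no cannabis". Under Patient allocation and blinding, participants take "cannabis or placebo oil once per day before bedtime for 12 weeks".

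**Entry.** Exclusion criteria lists, among other items, a known history of substance abuse, allergy or a suspected adverse reaction to cannabis, antibiotics in the preceding 3 months, NSAIDs, and probiotics or prebiotics. Current or recent use of cannabis oil is not listed. Patient enrollment and recruitment has the medical record searched for "current medication including chemotherapy regime and other herbal use", with no consequence attached.

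**Timing.** Visits and follow-ups places the eligibility check, consent and allocation at the first visit, where "the blood, saliva, stool, and skin samples will be collected as a baseline and start the treatment as day 1".

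**Outside cannabis.** The one instruction, in the same section, is "After the trial, patients will be asked to stop taking cannabis oil from any sources". The next sentence provides a further month of monitoring for withdrawal symptoms.

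**Availability.** Clinical practice in Thailand says that both study oils are government-made and on the National List of Essential Medicines. The Discussion describes "medical cannabis to be available on prescription to patients for approved conditions like cancer chemotherapy for relief of pain".

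**Measurement.** "The kinetic concentrations of THC and CBD will be quantitatively measured in two visits"; Trial timepoints and Table 1 put these at weeks 0 and 6.

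**The concern.** The exclusion list is detailed. It removes users of several products that could disturb the microbiome or symptom results, one of them with a look-back window, but it leaves out use of the test substance itself. By the article's own account, women on chemotherapy can be prescribed that substance for pain, and pain is the primary outcome. A woman who tolerates prescribed cannabis oil meets none of the listed exclusions.

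Two things are at stake:

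- **The placebo contrast.** Outside cannabis used by placebo patients during the 12 weeks would shrink the week-12 pain difference. The analysis is by intention to treat, which rightly keeps these patients in their arm, so the lost contrast cannot be recovered in the primary analysis.
- **The baseline.** In a woman already using cannabis oil, the week-0 ESAS, microbiome, cytokine and THC/CBD values are measured on the drug. Statistical analysis plans paired before/after tests, and those comparisons would start from the wrong place.

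**Working it through.** There is no stated figure to reproduce. The check is a reading of the text, followed by a calculation for scale.

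**1. Can a current user enter?** A woman on prescribed cannabis oil, without allergy, adverse reaction or a history of substance abuse, meets no cannabis-related exclusion. The record search for herbal use and medication could reveal her use, but no action follows from it. The text admits her.

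**2. Is there an interval for a washout?** Eligibility check, consent, allocation, baseline sampling and day 1 fall at one visit. No cannabis-free interval is described, and a week-0 THC/CBD result would normally come too late to inform allocation.

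**3. Is outside use addressed during weeks 0-12?** The only instruction takes effect after the trial. The content listed for CRF02 (follow-up and adverse drug reaction, all four visits) in the Table 1 footnote names no item on outside use. It does name a pharmacokinetic record form, whose fields are not shown.

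**4. Could it be detected?** In part. THC/CBD blood is scheduled at weeks 0 and 6, and Table 1 makes no distinction by arm. No eligibility or analysis rule uses the results, and none is scheduled at week 12, the primary time point.

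**5. Scale, on assumptions.** The documents give no contamination rate. Let delta be the true difference between an active arm and an uncontaminated placebo arm. Let a share c of placebo patients take outside cannabis with the same effect, and suppose that outside use adds nothing in the active arm. Then:

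- placebo mean shift = c × delta
- difference retained = delta - c × delta = delta × (1-c)
- patients needed for the same power = 1/(1-c)² times as many
- power of a comparison that had 80% at two-sided 0.05 = Φ[(1.960 + 0.842) × (1-c) - 1.960]

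| c (assumed) | Difference retained | Patients needed | Power, from 80% |
|---|---|---|---|
| 10% | 90% | × 1.23 | 71% |
| 20% | 80% | × 1.56 | 61% |
| 30% | 70% | × 2.04 | 50% |
| 40% | 60% | × 2.78 | 39% |

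For example, at c = 20%: 1/0.8² = 1.56, and Φ(2.802 × 0.8 - 1.960) = Φ(0.28) = 61%.

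If a share a of active-arm patients also took outside oil and gained the same amount again, the retained difference would be delta × (1 - c + a). With a = c nothing is lost, so the table applies only when outside use matters in the placebo arm alone.

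**6. Margin.** Sample size estimation sets 30 per arm with up to 50% loss, which leaves 30 × (1 - 0.5) = 15 per arm. There is little room to absorb dilution.

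**The case against.** **This is a condensed article.** Rules on prohibited medication, CRF fields and patient instructions often sit in a full protocol that is not shown here. That is fair, and a rule may exist there. But the article does set out its exclusions item by item, and as written they admit current users. If a rule exists elsewhere, the remedy is to state it and reconcile the two.

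**The post-trial instruction belongs to the withdrawal-monitoring month.** This stands. A reader might infer from its timing that outside oil is allowed during the 12 weeks. The text does not say so; it is silent on that period.

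**Randomisation protects the primary comparison.** This also stands for prior use. A reader might infer that enrolling current users biases the week-12 comparison. Prior use is balanced across arms in expectation, so it does not do so by itself. Randomisation does not, however, repair the within-arm before/after comparisons or the PK baseline, and it does not prevent dilution from use after allocation.

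**The size is invented.** The share c is an assumption. The article's earlier pain change (0.95 ± 2.39) is an uncontrolled one-month change, not a between-arm effect, so it is not used here. It is plausible that placebo patients would seek outside oil more than others, but the documents do not support it, and patients on the lower-THC oil might seek it too.

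**Partial safeguards exist.** The record search, the substance-abuse exclusion and two scheduled drug-level samples make control incomplete, not absent. None is tied to a stated rule on cannabis use.

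**Conclusion.** The point holds in a limited form. The listed criteria do not exclude current or recent users of cannabis oil, and no stated rule covers outside cannabis during weeks 0-12, in a population that the article says can obtain it on prescription. The placebo arm may therefore be diluted towards no difference, and the week-0 samples may not be drug-free.

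The documents do not show that contamination will occur, and its size is unknown. The retained fraction (1-c) rests on three assumptions: outside use has the same effect as the trial oil, it matters only in the placebo arm, and c takes the values tried. The firmer consequence is for the before/after microbiome, cytokine and symptom comparisons and for the PK baseline, where any current user enters with an exposed baseline whichever arm she is in.

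This is worth settling before enrolment, because neither an exposed baseline nor a diluted placebo arm can be restored afterwards.

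**What to change.** 1. **Eligibility.** Add a criterion on cannabis or cannabinoid use before week 0, with the look-back length set by the investigators. Check it before allocation, using the patient's history and the record search already planned.
2. **Rule during treatment.** State the rule that applies to outside cannabis in weeks 0-12, so that Visits and follow-ups is reconciled with the cannabis versus no-cannabis contrast in Summary of the study. What that rule should be is for the investigators.
3. **Recording.** Add an item on outside cannabis use to CRF02 at weeks 1, 6 and 12.
4. **Use of the scheduled assays.** Prespecify that THC or CBD found at week 0 (any arm) or at week 6 (placebo arm) flags contamination. Keep the week-6 results from blinded staff, since they can reveal the arm.
5. **Analysis.** Keep flagged patients in the intention-to-treat analysis, and name one supportive analysis that allows for contamination. Simply dropping flagged placebo patients would break the randomised comparison.

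**Cost.** One criterion, one stated rule, one CRF item and a short analysis paragraph; the blood is already scheduled. Some current users become ineligible, in a number that the documents do not allow to be estimated. Exposure at week 12 would rest on self-report, because no THC/CBD sample is scheduled then.

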#### Trial timepoints

Assessment of adverse drug effects will be collected with 4 time points: 0th, 1st, 6th, 12nd weeks of the trial day. The pain symptoms, QoL and diet pattern will be recorded with 3 time points: 0th, 6th, 12nd weeks. The blood collection (3 mL) for pharmacokinetic and pharmacogenetic tests will be performed on 2 time points: 0th, 6th weeks. The blood (10 mL), feces, skin scrapping, and saliva samples will be taken for biochemistry tests (plasma/ serum), microbiome (gut/ skin/ saliva), cytokines (plasma) and bacterial metabolites (serum/ feces) will be analyzed at 2 time points: 0th, 12nd weeks. The overview of the tests and visits of the clinical trial was shown on the following Table 1.

**Table 1 Tab1:** SPIRIT schedule of enrolment and assessments

#	Timepoint	Week-0 baseline	Week-1 follow-up	Week-6 follow-up	Week-12 follow-up
		T1	T2	T3	T4
1	**Enrolment**				
	Eligibility screening	x			
	Informed consent	x			
	Allocation	x			
2	**Assessment**				
	CRF01 Case Record Form^a^	x			
	CRF02 FW & ADR^b^	x	x	x	x
	CRF03 ESAS	x		x	x
	CRF04 EQ-5D-5 L	x		x	x
	CRF05 Food Frequency Questionnaire	x		x	x
3	**Blood Samples, Serum**				
	Blood Chemistry^c^	x			x
	Cytokines^d^	x			x
	Bacterial Metabolites^e^	x			x
	Pharmacokinetics parameters	x		x	
	Pharmacogenetics parameters	x		x	
4	**Feces Samples**				
	Fecal Microbiome Profile	x			x
	Fecal Bile Acid Profile^f^	x			x
	Fecal SCFAs^g^ and BCFAs^h^	x			x
5	**Skin Samples**				
	Skin Microbiome Profile	x			x
6	**Saliva Samples**				
	Oral Microbiome Profile	x			x

^a^Demographic and Epidemiological Factors: age, weight, height, waist circumference, hip circumference, neck circumference, alcohol consumption, smoking status, occupation, monthly income, method of health payment, and highest education

^b^Follow up and adverse drug reaction: vital signs, physical examination, lab results to assess liver, kidney and heart function, pharmacokinetic record form, drug tolerance assessment form, and adverse event assessment form

^c^Blood Chemistry: lipid profile, liver function test (LFT)

^d^Cytokines: interleukin-17, interferon-gamma, Interleukin-10, tumor growth factor-beta

^e^Bacterial Metabolites: lipopolysaccharide binding protein, sCD14 levels, equol, cadaverine

^f^Fecal Bile Acid Profile: chenodeoxycholic acid, deoxycholic acid, lithocholic acid

^g^SCFAs: butyric acid, propionic acid, acetic acid

^h^BCFAs: iso-butyric acid

### Primary outcome measures

The pain level of each patient will be assessed using the ESAS form at the last visit as primary outcome.

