### Clinical practice in Thailand

Currently, the Herb and Thai Traditional Medicine Development Division, Department of Thai Traditional and Alternative Medicine (DTAM), Ministry of Public Health, Thailand, manufactures Metta Osot (THC 81 mg/ml; THC 3 mg/drop) and Ganja Oil (THC 2 mg/ml; THC 0.08 mg/drop and CBD 0.02 mg/drop), both of which are produced under license number 13/2562 and has been added to the National List of Essential Medicines [28]. The preliminary analysis of the Thai Cannabis Practice Patterns and QoL (Thai Cannabis PQ) study assessed the pain symptoms using the ESAS and QoL using the EuroQoL Group’s 5-dimension, 5-level (EQ-5D-5 L). It revealed that QoL and all ESAS symptoms improved significantly at 1 month (*p* < 0.001), of which feeling of wellbeing (1.00 ± 2.34), pain (0.95 ± 2.39), tiredness (0.93 ± 2.51), and anxiety (0.85 ± 2.25) showed the largest mean differences [29].

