## Materials and methods

### Target population

We include 90 adult breast cancer women patients who were diagnosed with breast cancer or currently receiving chemotherapy at King Chulalongkorn Memorial Hospital (KCMH) with an anticipated starting recruitment approximately in August 2023. The sample size was calculated using the mean ESAS values of the previous study [29].

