### Statistical considerations

#### Sample size estimation

We target 30 patients in each arm, considering the maximum follow-up loss of 50%. Since the target population is metastatic breast cancer cases, questionnaires and biological samples such as blood, stool, saliva, and breast skin scrapping will be collected before and after the treatment, which could increase the withdrawal rate at any time during the trial.

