#### Statistical analysis

The data collected from different questionnaires, including case report forms, will be prepared in Microsoft Excel, followed by data cleaning and extraction. The statistical analysis will be performed on an intention-to-treat basis using Stata/MP software version 16.0 (StataCorp 2017, College Station, TX). Descriptive statistics like pair t-tests for before and after-treatment groups will be carried out using mean with standard deviation for normally distributed continuous data and median with interquartile range for non-normal distributed continuous data. Categorical data will be presented as counts and percentages using the Chi-square test. Continuous data will be assessed for normal distribution using a histogram and Shapiro–Wilk test. One-way ANOVA with Bonferroni correction will be used for normally distributed continuous data, and the Kruskal-Wallis test will be used for non-normal distributed continuous data among 3 arms.

To identify the alpha diversity, Shannon’s diversity index is used for evenness and Chao 1 index for the richness of operational taxonomic units (OTUs). The Jaccard dissimilarity index is used to detect beta diversity, and it is statistically described by permutational multivariate analysis of variance using distance matrices (PERMANOVA) test. A statistically significant level is defined as *p* < 0.05. Correction for multiple analyses was not done, but they will not be included in the conclusion of the study as factual findings. Sensitivity analysis using some subgroup to show robustness will be considered if the primary outcome is statistical significance.

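### Week-12 ESAS pain is the primary outcome, but entry requires no pain and the week-0 score neither selects nor stratifies women, which risks a floor effect of unknown size

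*Protocol article*

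**What the plan says.** - **Outcome.** Primary outcome measures: "The pain level of each patient will be assessed using the ESAS form at the last visit as primary outcome". Summary of the study gives the matching aim: "We aim to determine the intensity of the pain and QoL experienced by cancer patients".
- **Entry.** The Inclusion criteria list women aged 18 to 70 with breast cancer of any stage, starting or already on chemotherapy, at the one hospital. No item mentions pain, a symptom score or need for analgesia. The Exclusion criteria rule out NSAID users, in the same item as recent antibiotic use and next to the item on probiotics and prebiotics. No other analgesic is named.
- **Target population.** Sample size estimation describes it differently: "Since the target population is metastatic breast cancer cases".
- **Week-0 score.** Table 1 places eligibility screening, allocation and ESAS all at week 0. Secondary outcome measures lists the week-0 ESAS as a secondary outcome.
- **Allocation.** Patient allocation and blinding: "The allocation will be conducted with a 1:1:1 ratio using block randomization", with blocks of six. No stratification factor is named.
- **Analysis.** Statistical analysis compares the three arms by one-way ANOVA with Bonferroni correction, or by Kruskal-Wallis if the data are not normal.
- **Size.** Target population: "The sample size was calculated using the mean ESAS values of the previous study [29"]. Sample size estimation: "We target 30 patients in each arm, considering the maximum follow-up loss of 50" per cent.

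**The concern.** Eligibility and the primary outcome are both fixed in the article, and they do not fit together well. A woman who scores 0 for pain at week 0 is eligible. So is a woman who has not yet started chemotherapy and may have no treatment-related pain. Taking 0 as the bottom of the pain item, such women cannot improve on their entry score. If they also stay near 0 on placebo, they add patients without adding contrast between arms, and they pile tied scores at zero in the ANOVA or Kruskal-Wallis comparison.

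The effect expected from the earlier work may also not carry over. The pain change reported under Clinical practice in Thailand comes from an observational cohort of patients receiving Thai cannabis oil in routine care. Nothing shows that women with any stage of breast cancer on chemotherapy start with comparable pain. At stake is the sensitivity of a small trial's main comparison, although the form that could protect it is already scheduled at the allocation visit.

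**Working it through.** **Reproducing the plan's figure.** With up to 50% loss, 30 per arm leaves 30 × (1 − 0.5) = 15 evaluable, and 3 × 30 = 90 in total. The dropout arithmetic is consistent. The 15 itself cannot be rebuilt, because the article states neither power nor a target difference. The point below does not depend on it.

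**Inputs for an illustration.**
- Effect d = 0.95 and SD s = 2.39, from Clinical practice in Thailand ("pain (0.95 ± 2.39"). This is an uncontrolled within-patient change at 1 month. It stands in here for a between-arm difference and its SD, as if the whole change were drug effect.
- Two-sided 5% level: Statistical analysis sets the threshold at p < 0.05, and two-sidedness is my assumption. Power of 80% is also assumed.
- Share f of women who are pain-free and contribute no difference between arms. The documents give no value, so 20%, 30% and 50% are assumed.

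**Formulas.**
- Diluted difference: d × (1 − f).
- Evaluable patients per arm: 2 × (1.96 + 0.842)² × variance / difference².
- Variance, SD fixed: 2.39² = 5.712.
- Variance, SD shrinking (pain-free women add no spread): (1 − f) × 2.39² + f(1 − f) × 0.95².

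**Results.** With f = 0: 2 × 7.85 × 5.712 / 0.9025 gives 100 per arm after rounding up.

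| f | Difference | n per arm, SD fixed | Ratio | Shrunken SD | n per arm, SD shrinking | Ratio |
|---|---|---|---|---|---|---|
| 0 | 0.95 | 100 | 1.0 | 2.39 | 100 | 1.0 |
| 20% | 0.76 | 156 | 1.6 | 2.17 | 129 | 1.3 |
| 30% | 0.665 | 203 | 2.0 | 2.05 | 149 | 1.5 |
| 50% | 0.475 | 398 | 4.0 | 1.76 | 215 | 2.2 |

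With SD fixed, the ratio is simply 1/(1 − f)².

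**Power at the planned size.** For one pairwise comparison at 0.05 without Bonferroni (normal approximation), with 15 evaluable per arm and f = 0: 0.95 / (2.39 × √(2/15)) = 1.089, and the probability below 1.089 − 1.96 = −0.871 is about 19%. With all 30 per arm it is about 34%. At 15 per arm, power falls to 14–16% for f = 20%, 12–14% for f = 30% and 8–11% for f = 50%. Dilution makes a weak comparison weaker, but most of the shortfall is there before any floor effect.

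**The case against.** The strongest case on the other side is that not requiring pain at entry is a design choice. The Conclusions present the aim mainly as relief of chemotherapy-related side effects, so preventing pain counts as much as relieving it. Baseline adjustment may also sit in an analysis plan that is not shown. Several stronger readings are tempting and should not be drawn:

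- **That the objective is blocked.** The outcome is the week-12 level, not relief from baseline. A woman who enters at 0 and develops less pain on oil than she would have on placebo contributes to the contrast.
- **That a null result could not be interpreted.** ESAS is recorded at week 0, so the baseline distribution will be known.
- **That the NSAID exclusion removes many women in pain and lowers the sample's pain.** NSAID use is not quantified and users of other analgesics remain eligible. The direction is also unclear, since a woman controlled on NSAIDs may score low. Its position suggests a microbiome purpose, though no reason is given.
- **That 1.6, 2.0 and 4.0 are estimates of the loss.** They hold the SD fixed, whereas scores piled at zero would shrink it. The 0.95 is a whole-cohort mean that may already include pain-free patients, so applying (1 − f) may dilute it twice.
- **That the sample will have little pain.** The sample-size text speaks of metastatic disease, which may imply otherwise. The article does not settle which population is meant.

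These points limit the wording and the size of the concern. They do not remove the mismatch: a trial run exactly as the article describes would admit pain-free women and make no use of their week-0 score at entry or allocation.

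**Conclusion.** The point holds as a risk of dilution. The article makes week-12 pain the primary outcome, sets no pain requirement at entry, and uses the week-0 ESAS neither to select nor to stratify. How much sensitivity is lost cannot be estimated from the documents, because no baseline pain distribution is given and the population is described in two ways.

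The range in the table rests on an assumed pain-free share, on such women showing no difference at all, and on a borrowed within-patient SD. It shows direction and order of size only. Changing eligibility would not by itself bring the trial to 80% power for a 0.95-point difference. The change is worth making because it is cheap, but its absence does not invalidate the trial.

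**What to change.** Complete the week-0 ESAS before allocation, then take one of two routes.

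1. **Select.** Add an inclusion criterion with a stated minimum ESAS pain score, at the least above 0. A threshold of just above 0 still admits women close to the floor, so the sponsor should justify the value chosen. The cost is slower recruitment.
2. **Stratify.** Keep all women, stratify allocation by week-0 pain (none versus any), account for that stratum and for baseline pain in the primary week-12 comparison, and pre-specify the comparison in women with week-0 pain above 0. Every woman stays in for the microbiome, quality-of-life and pharmacokinetic aims. The cost is one more stratum and a smaller pain subset: if half were pain-free, 30 × 0.5 = 15 per arm randomised, or 7 to 8 after the planned 50% loss.

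If recruitment is already under way, the baseline-adjusted comparison and the pain-above-0 comparison can still be specified before unblinding.

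In either case, reconcile the any-stage wording of the Inclusion criteria with the metastatic population named under Sample size estimation, since this sets the baseline pain to expect. Also state how the NSAID exclusion fits a pain endpoint. Both are text changes.
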